### Data analytic plan

Within-patient standardized effect size information (i.e., Cohen’s d and 95% confidence intervals) from baseline to 3-month follow-up will be calculated for LOC-E episodes and all secondary outcomes. Clinical outcome data will be analysed for all youth who remain on a stimulant for the 3-month duration. Descriptive statistics (e.g., means and standard deviations) will be used to report demographic information, medication doses, adverse events, and frequency of medication discontinuation. If available, reasons for medication discontinuation and loss to follow-up will be documented. Given the case series design, there will be no a priori power analysis.

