### Participants

We will collect data on forty 8–13-year-old youth and their parents. The study will use a prospective cohort sample from the Atlantic ADHD Centre in Dartmouth, Nova Scotia. To be eligible for inclusion, youth must (A) meet the diagnostic criteria for ADHD, and (B) have experienced at least 3 episodes of LOC-E during the past 3 months^1^, accompanied by some degree of distress and 2 of the 5 behavioral symptoms associated with LOC-E. Inherent to the definition of LOC-E, consumption of an abnormally large amount of food will not be required. Further details related to the diagnostic assessment for ADHD and LOC-E are provided in later sections. Participants will be excluded if they are (a) currently receiving psychotherapy treatments for ADHD, eating disorders, or obesity, and/or (b) undergoing concurrent medication changes that could affect ADHD or eating related symptoms (as determined by psychiatrist and principal investigator [[name]]). Participants must also have sufficient language skills and a general practitioner to initiate the stimulant and monitor adverse events.

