The EDE 17.0D [35], which measures eating disorder symptom severity, has been adapted for use with children ages 8 and above [36, 37]. The ChEDE has been shown to have high inter-rater reliability and internal consistency [38, 39]. For the purposes of this study, only diagnostic item 11 (identifying bulimic episodes and other episodes of overeating) of the ChEDE will be used, which includes questions regarding feelings of loss of control over eating, features associated with binge eating, and distress about binge eating. The measure will be used for diagnostic assessment of LOC-E for study inclusion purposes, and at a baseline and 3-month follow-up to establish LOC-E episode frequency. The ChEDE will be administered by well trained research assistants tasked to develop positive rapport with the children and ensure concepts are explained in a manner that is developmentally appropriate to each child [see 40 for a detailed description]. Also, parents will remain present during the assessment in case the children need assistance understanding the interviewer.

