### Primary outcome

LOC-E episode frequency in the last 3-months is the primary outcome of this study, as measured by the ChEDE.

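### The primary outcome is an episode count, but its only stated effect measure is a Cohen's d with no named SD, which does not identify the reduction in episodes

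*Protocol article*

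**What the plan says.** In the protocol article, the Primary outcome section reads "LOC-E episode frequency in the last 3-months is the primary outcome of this study, as measured by the ChEDE". Under Participants, a child must "have experienced at least 3 episodes of LOC-E during the past 3 months". The Procedure section has this confirmed with the ChEDE at a screening visit, and baseline is a separate, later interview before the stimulant is started. The same ChEDE item therefore serves for eligibility, baseline and follow-up.

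The Data analytic plan names one effect measure for every outcome, a within-patient Cohen's d with "95% confidence intervals) from baseline to 3-month follow-up will be calculated for LOC-E episodes and all secondary outcomes". It does not name the standardising SD (change, baseline or averaged) or the interval method. Its descriptive statistics "will be used to report demographic information, medication doses, adverse events, and frequency of medication discontinuation"; LOC-E episodes are not in that list. The planned sample is 40, and outcomes are analysed only for children still on a stimulant at 3 months, so at most 40 contribute. There is no power analysis. The Discussion suggests that the effect sizes might feed the sample-size calculation of later trials.

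**The concern.** A count of episodes has a natural unit and a floor at zero, and often a long right tail. Cohen's d divides the mean change by an SD, and in a skewed count a few high-frequency children largely set that SD. Two samples with the same proportional fall can then show very different d values, and the same d can stand for very different falls.

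This matters more here than it would in a trial with a test and a decision. The study has no hypothesis test, so the effect size is its main product. A later trialist would want the expected number of episodes under treatment, or the share of children who stop having them. A pre-post d with an unnamed SD gives neither.

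**Working it through.** **Inputs from the protocol article.** Count outcome over 3 months; entry at 3 or more episodes; n = 40; 95% intervals (taken as two-sided). It gives no mean, SD, skewness or share of zeros for the count, and no target effect, so there is no planned figure to reproduce. Every distributional input below is an assumption.

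**Step 1: the arithmetic of d.** Let the mean fall from 10 to 5 episodes, a 50% reduction, and let d_av = mean change / √[(SD₀² + SD₁²)/2].

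- SDs 5 and 5: 5/√25 = 1.00
- SDs 10 and 8: 5/√82 = 0.55
- SDs 20 and 15: 5/√312.5 = 0.28

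**Step 2: simulated counts.** Child rates are gamma with the mean per 3 months and shape shown. Visit-to-visit gamma noise has variance 0.25 or 1. Counts are Poisson, children are kept if the entry count is 3 or more, and the true rate is halved in every child. The entry count stands in for baseline, which is a simplification because the actual baseline is a later interview.

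| Rate mean, shape | Noise | Mean episodes | Ratio | d, change SD | d, average SD | d, baseline SD |
|---|---|---|---|---|---|---|
| 8, 20 | 0.25 | 8.9 → 4.1 | 0.46 | 0.86 | 1.16 | 0.96 |
| 8, 2 | 0.25 | 10.2 → 4.7 | 0.46 | 0.74 | 0.85 | 0.69 |
| 8, 1 | 0.25 | 11.7 → 5.5 | 0.47 | 0.67 | 0.72 | 0.58 |
| 15, 0.5 | 0.25 | 23.0 → 11.2 | 0.49 | 0.53 | 0.52 | 0.41 |
| 8, 20 | 1 | 11.1 → 4.1 | 0.37 | 0.71 | 0.99 | 0.79 |
| 8, 2 | 1 | 12.5 → 4.8 | 0.38 | 0.58 | 0.75 | 0.60 |
| 8, 1 | 1 | 14.2 → 5.6 | 0.39 | 0.51 | 0.64 | 0.51 |
| 15, 0.5 | 1 | 26.6 → 11.8 | 0.44 | 0.37 | 0.45 | 0.35 |

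At the lower noise the ratio stays within 0.46–0.49, while change-SD d varies by a factor of 0.86/0.53 = 1.6 and average-SD d by 1.16/0.52 = 2.2. Runs that also varied the response between children gave change-SD d from about 0.42 to 1.15 for a true 50% reduction, with the ratio at 0.46–0.50.

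**Step 3: the reverse direction.** An average-SD d of about 0.5 matched observed reductions of 27%, 35%, 39%, 47% and 51% as the spread between children rose (from 8.9 → 6.5 to 23.1 → 11.3 episodes).

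**Step 4: the unnamed SD.** In the first row, choosing the change or the average SD moves d from 0.86 to 1.16, a shift of 0.30. The sampling half-width for d = 0.86 at n = 40 is 1.96 × √(1/40 + 0.86²/80) = 0.36, so the unstated choice is worth nearly as much as the sampling error. Sample size scales with 1/d². Used unconverted in a power calculation, the two values differ by (1.16/0.86)² = 1.8-fold.

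**Step 5: interval coverage.** The large-sample SE is √(1/n + d²/2n) for change-SD d and √(2(1−r)/n + d²/2n) for the other two, where r is the baseline–follow-up correlation. At n = 40, with a common proportional cut and with or without 40% full remission, nominal 95% intervals covered about 0.92–0.98 (change SD), 0.91–0.98 (average SD) and 0.90–0.996 (baseline SD). A robust interval for the ratio covered about 0.91–0.95. When responses also varied between children, d covered about 0.78–0.99 and the ratio 0.89–0.95. Values below 0.80 arose only with a low mean rate (3 per 3 months), a 50% reduction and very variable response (gamma shape 0.4).

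**Step 6: selection.** With no true change, mean episodes still fell by 2–9% at the lower noise and 11–27% at the higher. The ratio carries this as much as d does; that is why its values above sit below the true 0.50.

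**The case against.** The best counter-case has four parts.

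- **Over-dispersion is assumed.** This stands. The protocol gives no dispersion figure, so the size of the effect on d is conditional. Step 1, however, needs only that SDs differ between samples.
- **The intervals are mostly acceptable.** This largely stands. A reader might infer that the planned intervals are unreliable and that a count-based interval would repair them. The calculations do not support that: departures run both ways, the severe ones need an extreme scenario, and d is often as close to nominal as the ratio or closer.
- **Baseline is not cut at 3.** This stands. A reader might infer that the analysed baseline count is truncated, but the threshold applies at screening and baseline is a later interview. Selection still acts through the correlation between the two, and no choice of effect measure removes it.
- **An article condenses, and the stakes are low.** This stands in part. Tables of raw means or medians may sit in a fuller document, and nothing in the article rules them out, so it would be wrong to say that the reduction will be unrecoverable. The design is a case series with acknowledged limits and no test. But the choice of d as the effect measure for every outcome is stated, not omitted, and that choice is what is at issue.

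**Conclusion.** The concern holds as a criticism of the effect measure. For the 3-month episode count, d alone does not identify the reduction: about 0.4 to 1.15 for the same true 50% fall under assumed skewed counts. The unnamed SD adds an ambiguity nearly as large as the sampling half-width in one assumed sample. This makes d a weak basis for planning a later trial.

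The claim about intervals is secondary and conditional. Coverage may depart from 95% in either direction (about 78–99% in the assumed scenarios), and a robust ratio interval, at about 89–95%, is not uniformly better calibrated. The case for the ratio is that it can be read as a reduction, not that its coverage is superior. All magnitudes rest on gamma-Poisson counts, the stated noise and response patterns, and the entry count standing in for baseline.

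**What to change.** For LOC-E episodes, make the follow-up/baseline ratio of episodes the main summary, with a paired robust interval or a bootstrap that resamples children. Add the median change and the proportion of children with zero episodes at 3 months. These also show whether a few high-frequency children drive the ratio. If d is kept for this outcome, state which SD it uses and bootstrap its interval. Keep d for the rating scales.

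The cost is a sentence or two in the Data analytic plan and a little programming, with no new data. The downside is that the primary outcome no longer shares one scale with the secondary outcomes. The change does not cure regression to the mean from selecting children on the outcome, so that caveat should accompany the ratio.

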## Discussion

This will be the first study to prospectively examine the effect of stimulants on LOC-E in youth. The limitations of this observational design include the inability to control for placebo or time effects and other confounding variables (e.g., variation in medication type and dose). Other limitations include the small sample size, short treatment duration, and risk of self-report, assessment, and recall biases (especially given the age of our sample).

Those limitations notwithstanding, this study explores a novel intervention that could lead to important future research. If our results show that stimulants are associated with a decrease in LOC-E over 3-months, the effect size data could be used for a power calculation in future clinical trials. A hypothetical future direction could include a two-phase randomized controlled trial to compare a group of youth with comorbid ADHD and LOC-E treated with a psychotherapeutic intervention to a group treated with a stimulant only. If the psychotherapy group continues to experience LOC-E after the initial treatment phase, the unremitted patients could be crossed over into a stimulant phase to examine whether stimulants benefit individuals who do not respond to psychotherapy.

Investigating stimulants as a possible adjunct for psychotherapy is relevant because only 40–50% of adults treated for LOC-E (or binge eating) remit with psychological treatments alone [53]. In one of the few psychotherapy trials for pre-adolescent children with LOC-E, about 40% continued to experience LOC-E after a family-based therapy [54]. One explanation for inadequate response to psychotherapy is that LOC-E is caused by multiple factors, which vary amongst individuals; and therefore, current psychotherapies may not target *all* the putative causal mechanisms. Byrne et al. [8] describe a domain summary of factors related to pediatric LOC-E that includes: (a) genetic/physiological (e.g., hormonal, family history of obesity, neural functioning), (b) socioenvironmental (e.g., dieting, media thin-ideal, peer/family pressure to be thin), (c) psychological (e.g., negative affect, emotion dysregulation, attentional biases, executive function impairment), and (d) behavioral (e.g., impulsivity, intake of energy-dense foods). Within these domains, stimulant medication as an adjunctive treatment may be effective in relation to mechanisms such as neural functioning, executive function impairment, and impulsivity—especially in youth with impairments in these areas (e.g., those with ADHD). Relatedly, another strength of this study is the preliminary exploration of several of these mechanisms. Specifically, the secondary outcomes related to impulsivity, eating-related cognitions, emotions and behaviors, and mood/anxiety will provide pilot data for future studies that examine not only treatment effect, but also underlying mechanisms associated with LOC-E.

## Data Availability

Not applicable.

## List of abbreviations

ADHD: Attention deficit/hyperactivity disorder
BED: Binge-eating disorder
BIS/BAS: Behavioral inhibition system/behavioral activation system scales
CBBEQ: Children’s brief binge-eating questionnaire
CEBQ: Child eating behavior questionnaire
ChEDE: Eating disorder examination – child version C.1
ChEDE-Q8: Eating disorder examination-questionnaire adapted for children, short form
LOC-E: Loss of control eating
RCADS-25: Revised child anxiety and depression scale – short version
VADPRS: Vanderbilt ADHD diagnostic parent rating scale
